### Data collection and management

The authors employ a web-based clinical research management system (Healthroad, Seoul, Republic of Korea), which gathers clinical data and information through on-line (konclude.e-trial.co.kr, Fig. 2). Principal investigators or clinical research coordinators in each site should sign up and enter clinical data onto an eCRF. Approved researchers of central data managing institution will manage the data and information. Only the principal investigator can access the final trial dataset and analyze them. Personal information of enrolled patients will be maintained for 5 years in order to protect confidentiality.

**Fig. 2 Fig2:**
[figure not shown]
The electronic case report form on line

### Drop-out

A patient can be dropped out in cases as follows:Not acceptable adverse events related to surgery or chemotherapyDifferent treatment needs which not approved in this trialA patient’s refusal by any reasonsA patient’s pregnancy

### Statistical analysis

Continuous variables will be analyzed with independent two sample t-test, whereas categorical variables will be analyzed with Chi-square test or Fisher’s exact test. 3-yr DFS will be analyzed with Kaplan-Meier curve. The difference between both Arms will be compared by Cox’s proportional hazards model. Interim analysis for pCR will be performed after TME of the last enrolled patient with Cochran-Mantel-Haenszel test. *P*-value less than 0.05 will be considered as significant. All analyses will be performed with SPSS version 20.0.

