### Sample size calculation and randomization

Based on literatures, pCR rates and 3-year DFS after CRT for rectal cancer were known to be 10 to 28% and 50-65%, respectively [2, 6, 8–13]. Thus we hypothesize that the experimental arm would show a 15% improvement in pCR and in 3-year DFS, compared with the control arm (15 to 30% and 65 to 80%, respectively). The accrual period is 2 years and the follow-up period is 3 years. Based on the superiority design, one-sided proportion test and log-rank test with α-error of 0.025 and a power of 90% was conducted for both primary endpoints: pCR and 3-year DFS. The pCR of each group was considered to be 15 and 30%, and the 3-year DFS of each group was considered to be 65 and 80% assuming that accrual time was 2 years and follow up time was 3 years. Allowing neoadjuvant CRT for a drop-out rate of 10%, 358 patients (179 per arm) for pCR and 316 patients (158 per arm) for 3-year DFS will need to be recruited. Therefore a total of 358 participants (among 358 and 316) are needed. This study of 358 participants had at least 81% power (90% each = 0.9, so 0.9 × 0.9 = 0.81) to simultaneously detect a difference of pCR and 3-year DFS of two groups. Randomization will be performed in a 1:1 ratio by computer-generated random numbers, with the use of stratified permuted 4 blocks. It will stratified according to age (< 70 vs. ≥70), clinical T stage (T1/2 or T3), and clinical N stage (N0 or N1/2). Among 8 strata, 2 strata will not be used because clinical T1/2 N0 (age < 70 and ≥ 70) are not indicated for neoadjuvant CRT.

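### The DFS Cox model and the CMH test for pCR do not name the factors used to stratify randomisation; naming age, cT and cN in both is a small, nearly free improvement

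*Protocol article*

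**What the plan says.** All references are to the protocol article.

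- **Randomisation** (Sample size calculation and randomization; also Study design): 1:1 allocation "with the use of stratified permuted 4 blocks". The factors are age (<70 or ≥70), clinical T stage (T1/2 or T3) and clinical N stage (N0 or N1/2). Of the 8 possible strata, the 2 with cT1/2N0 are not used, which leaves 6.
- **DFS analysis** (Statistical analysis): Kaplan-Meier curves, and "The difference between both Arms will be compared by Cox"'s proportional hazards model. Only the arms are mentioned. The text does not say whether the model is stratified, adjusted or neither.
- **pCR analysis** (same section): after TME of the last enrolled patient, "with Cochran-Mantel-Haenszel test". The stratifying variables are not named.
- **Design basis** (Sample size calculation and randomization): "one-sided proportion test and log-rank test with α-error of 0.025 and a power of 90% was conducted for both primary endpoints". For DFS, "the 3-year DFS of each group was considered to be 65 and 80"%, and "The accrual period is 2 years and the follow-up period is 3 years".

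**The concern.** Permuted blocks within strata force the arms to be nearly balanced on age, cT and cN. If those factors predict recurrence, the true sampling variability of the treatment comparison is smaller than under simple randomisation. A test that ignores the strata still uses the larger variance, so it rejects too rarely under the null. Leaving out prognostic covariates also pulls the marginal hazard ratio towards 1. Both effects are conservative. What is at stake is a little power on a primary endpoint.

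There is also a pre-specification point. With the factors unnamed, the DFS comparison could be run unadjusted, adjusted or stratified, giving somewhat different hazard ratios and p-values. That choice is best fixed before outcomes are seen.

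**Working it through.** **1. Reproduce the plan's sizes.**

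- Hazard ratio under exponential DFS: ln(0.80)/ln(0.65) = 0.518.
- Events (Schoenfeld, one-sided 0.025, 90% power): 4 × (1.960 + 1.282)² / (ln 0.518)² = 42.0/0.433 ≈ 97.1, so 98.
- Event probability with 2 years' uniform accrual and 3 further years of follow-up: 1 − [exp(−3λ) − exp(−5λ)]/(2λ). With λ = −ln(0.65)/3 = 0.1436 this is 0.435; with λ = −ln(0.80)/3 = 0.0744 it is 0.257. The mean is 0.3458.
- Patients: 98/0.3458/2 = 141.7, so 142 per arm; 142/0.9 = 157.8, so **158 per arm**, as stated.
- pCR, 15% against 30%, same error rates, no continuity correction: 161 per arm; 161/0.9 = 178.9, so **179 per arm**, as stated.

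**2. DFS power at the size adopted.** pCR sets the total at 358, or about 358 × 0.9 = 322 evaluable. Expected DFS events are 322 × 0.3458 = 111.4. Power is Φ(√(111.4/4) × 0.658 − 1.960) = Φ(1.51) = 93.5%, against a planned 90%.

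**3. Effect of leaving the strata out.** The documents give neither stratum shares nor prognostic effects, so both are assumptions:

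- Shares: 20% aged ≥70; 10% cT1/2N+, 25% cT3N0, 65% cT3N+.
- Baseline and treatment effect set so that overall 3-year DFS is 65% and 80%.
- 322 patients, blocks of 4 within six strata, 8,000 trials per row, score (log-rank) tests at one-sided 0.025.

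| Assumed HR for age / N / T | Type I error, unstratified | Type I error, stratified | Power, unstratified | Power, stratified |
|---|---|---|---|---|
| 1 / 1 / 1 | 2.5% | 2.4% | 93.3% | 92.9% |
| 1.2 / 1.5 / 1.5 | 2.5% | 2.7% | 93.0% | 93.1% |
| 1.5 / 2 / 2 | 1.9% | 2.4% | 93.0% | 93.9% |
| 2 / 3 / 2 | 1.6% | 2.5% | 93.4% | 95.1% |

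The Monte Carlo standard error is about √(0.025 × 0.975/8000) = 0.17 points for type I error and √(0.93 × 0.07/8000) = 0.29 points for power. The first two rows therefore show no detectable difference. The last two show a real but small one: 93.9 − 93.0 = 0.9 points and 95.1 − 93.4 = 1.7 points of power.

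A separate simulation, also with 322 evaluable patients and six strata, gave type I error of about 1.8 to 2.2% unstratified against 2.4 to 2.6% stratified when the factors were prognostic. Its power gain was about 0.3 to 1.5 points.

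**4. Sparse strata.** Under the assumed shares, the stratum aged ≥70 with cT1/2N+ holds 0.20 × 0.10 × 322 ≈ 6 patients and about 6 × 0.3458 ≈ 2 events. It would add almost nothing to a fully stratified test. A covariate model needs three extra parameters against about 111 events.

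**The case against.** The strongest objection is that the document does not say the Cox model is unadjusted. This is a condensed article, and covariates and strata are commonly left to a full protocol or SAP. A Cox model can include the randomisation factors, so the stated method is compatible with the fix. This stands: a reader might infer that the trial has chosen an unadjusted DFS analysis, but the text is silent and does not show it.

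A reader might also infer that the two primary endpoints are deliberately treated differently, one stratified and one not. That is not shown either, because the CMH strata are unnamed too.

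A third tempting reading is that DFS power is wasted or drops below 90%. One simulation of 3,000 trials, with 161 per arm and hazard ratios of 2.0 for cT3N+ against cT3N0 and 1.5 for age ≥70, gave 89.4% unstratified and 90.5% stratified, with no stated stratum shares. With the same hazard ratios, the shares in the working and control 3-year DFS held at 65%, a further 3,000 trials gave 91.7% and 92.5%. The gap of about one point recurs; the shortfall below 90% does not.

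Finally, marginal and covariate-conditional hazard ratios are different estimands, so reporting a marginal one is not an error. That also stands.

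None of this removes the suggestion. The trial already stratifies on these factors, and using them in the primary analyses is a better method at almost no cost.

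**Conclusion.** The point holds as a minor improvement. If the DFS comparison is run with arm alone, it is conservative when age, cT and cN are prognostic: one-sided type I error of about 1.6 to 2.2% instead of 2.5%, and 0 to about 2 points less power. If the factors are weak or not prognostic, the difference is nil. There is no added false-positive risk, and the sample size stands.

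The direction of the effect is secure. Its size depends on assumed hazard ratios and stratum shares. The statement that DFS power exceeds 90% also assumes that every patient is followed until 3 years after accrual closes, the reading used above to reproduce 158 per arm at 90% power. If DFS were instead cut off at 3 years for each patient, the mean event probability would be (0.35 + 0.20)/2 = 0.275, giving 322 × 0.275 = 88.6 events and 87.2% power. That difference would come from the follow-up rule and not from the strata.

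**What to change.** State in the Statistical analysis section, before outcome data are examined, that the primary DFS test and hazard ratio account for age group, cT and cN. Choose one method in advance. Either will do:

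- a Cox model with arm plus the three factors as covariates, which avoids sparse strata; or
- a log-rank test and Cox model stratified by the three factors.

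Do not allow a switch between them that depends on how sparse the strata turn out to be. Name the same three factors as the strata of the CMH test for pCR.

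The cost is one or two sentences, since the factors are already recorded for randomisation. If they are not prognostic nothing is gained, and under full stratification a very small stratum contributes little information.

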### Safety evaluation and reporting of adverse effect

Adverse events and serious adverse events must be reported to protect patients. Radiotherapy-related toxicity, chemotherapy-related toxicity, and surgery-related morbidity will be recorded onto the eCRF. Serious adverse events will be reported every quarter of the year, whereas suspected, unexpected, serious, adverse reaction, which could result in death or life threatening, will be reported within 15 days from the detection by investigators.

### Data monitoring

A committee will be organized for trial supervision. All members of the committee are certified according to the course of good clinical practice in each institution. All process including data collection, record, and management will be monitored by them. The committee can advise and request the principal investigator to change some plans.

### Protocol modification

If needed, the protocol can be modified by communication and agreement of the principal investigator and trial participants with revising its version.

## Discussion

Despite fundamental role of 5-FU as neoadjuvant and adjuvant regimen for advanced colorectal cancer, addition of various cytotoxic agents has been tried to improve oncologic outcomes. Among them was oxaliplatin, a platinum analogue (Table 1). FOLFOX as adjuvant regimen for locally advanced rectal cancer showed superior DFS compared with 5-FU or capecitabine alone in ADORE trial and the German CAO/ARO/AIO-04 study [35, 36], although it failed to show better oncologic outcomes but more proportion of acute toxicity as neoadjuvant regimen [7, 17, 18]. Surgical and medical oncologists concluded that FOLFOX is only efficient as adjuvant setting, not neoadjuvant for rectal cancer. Then, can FOLFOX show higher pCR rates without increasing acute toxicity in the position between neoadjuvant and adjuvant? This is the point that KONCLUDE trial concentrates on.

**Table 1 Tab1:** pCR by adding Oxaliplatin to 5-FU for rectal cancer

Trial	*N*	Regimen	pCR rate
STAR-01	705	5-FU vs. 5-FU + Oxaliplatin	16% vs. 16% (*p* = 0.904)
ACCORD 12	598	Capecitabine vs. CAPOX	13.9% vs. 19.2% (*p* = 0.09)
NSABP R-04	1608	5-FU vs. 5-FU + Oxaliplatin vs. Capecitabine vs. CAPOX	17.8% vs. 19.5% (*p* = 0.42)
CAO/ARO/AIO-04	1236	5-FU vs. 5-FU + Oxaliplatin	13% vs. 17% (*p* = 0.031)
PETACC-6	1094	Capecitabine vs. CAPOX	11.3% vs. 13.3% (*p* = 0.31)
Dellas et al.	70	CAPOX + Bevacizumab	17.4%
EXPERT-C	165	CAPOX vs CAPOX + Cetuximab	7% vs. 11% (*p* = 0.714)

*pCR* pathologic complete response, *5-FU* 5-fluorouracil, *CAPOX* capecitabine with oxaliplatin

As aforementioned, several authors already reported high pCR rates from consolidation chemotherapy without significantly increasing toxicity, while a couple of trials are on-going [21–25]. However, there were a few, but meaningful limitations in their studies including characters of phase 2 trial, variation of the resting period between radiotherapy and TME, and difference of total cycles of chemotherapy. These studies cannot establish the treatment guideline because of their inherited bias. Therefore, we adjusted total cycles of chemotherapy as 8 cycles of mFOLFOX6 to avoid inherited bias due to different cycles of chemotherapy. Moreover, we fixed the interval between radiotherapy and TME as 9 weeks, according to previous literatures which commented appropriate resting period as 6 to 12 weeks, to investigate efficacy of consolidation without confounding of various duration of interval from completion of CRT to TME.

KONCLUDE trial started with the first enrollment in December 7, 2016 after the registration on clinicaltrials.gov in July 25, 2016 (NCT02843191). We expect that this trial will conclude whether consolidation chemotherapy would attain higher pCR and improved DFS or not, providing a critical clue to establish the standard treatment in locally advanced mid- or low rectal cancer with level 1 evidence.

## Abbreviations

5-FU: 5-fluorouracil
CRT: chemoradiotherapy
DFS: disease-free survival
eCRF: electronic case report form
FOLFOX: 5-FU and leucovorin with oxaliplatin
KONCLUDE: Korean society of coloproctology trial of cONsolidation Chemotherapy for Locally advanced mid or low rectal cancer after neoadjUvant concurrent chemoraDiothErapy: a multicenter, randomized controlled trial
pCR: pathologic complete response
TME: total mesorectal excision
